### Allocation procedure

Randomization will be based on computer generated coding. Codes will be kept in sealed envelopes. These will be opened in the operating room by an anesthesiologist not involved in subsequent data accumulation or analysis. Patients randomized to the intervention arm will be subjected to brief periods of upper limb ischemia designed to induce RIPC, as described later. Patients assigned to the control arm will receive no ischemic preconditioning. Surgeons and intensive care physicians will be unaware of treatment allocation.

### Intervention and control protocols

Remote ischemic preconditioning will be induced by alternating periods of upper limb ischemia and reperfusion. Transient arm ischemia will be produced by inflating a blood pressure cuff to 200 mmHg for 5 min, and then deflating it for 5 min. This sequence will be repeated three times after the induction of anesthesia and prior to the surgical incision. Our intervention protocol has been used previously and constitutes a validated protocol with beneficial effects exerted at the myocardial level [9]. Patients in the control group will also have a blood pressure cuff placed, but it will not undergo the aforementioned inflation-and-deflation cycles.

### Myocardial revascularization

Morphine and diazepam will be administered to patients preoperatively. Induction and maintenance of anesthesia will rely on a combination of midazolam, sufentanil, pancuronium bromide, and sevoflurane. Propofol will be avoided, owing to its potential for inhibiting RIPC-inducing pathways [9].

Coronary revascularization will be performed via a median sternotomy with the use of cardiopulmonary bypass. Systemic heparinization with a target activated clotting time >450 s will be utilized. Both distal coronary and proximal anastomoses will be performed during a single period of aortic cross-clamping, thereby reducing the embolic burden related to aortic manipulation. Myocardial protection will be based on administration of both antegrade and retrograde cardioplegia. In the immediate period after cardiopulmonary bypass, a goal-oriented strategy targeting a cardiac index of 2.2 l/(min m^2^) will be employed. Interventions to attain this goal will include optimization of preload and, if necessary, inotropic support. The preferred inotropic agent in our institution is dobutamine. In the unlikely event that further escalation of vasoactive support is required, our armamentarium also includes phosphodiesterase 3 inhibitors, intra-aortic balloon pumps, and mechanical circulatory assistance. Full heparin reversal with protamine will be employed.

### Blood sampling

Venous blood samples for the measurement of troponin T will be taken on postoperative day 1. We will employ the Elecsys® Troponin T high-sensitive assay (Roche, Basel, Switzerland).

### Perioperative management

Postoperative medications will typically include a beta-blocker, a hydroxy-methyl-glutaryl-CoA reductase inhibitor and a diuretic. Aspirin (300 mg) will be administered within 6 hours of surgery, provided that the chest tube output is minimal. The use of angiotensin-converting-enzyme inhibitors postoperatively will be individualized and tailored to effect. Peptic ulcer prophylaxis will be universally implemented in the perioperative period, and continued for six weeks.

### Neurocognitive testing

Neurocognition in study patients will be evaluated using the Montreal Cognitive Assessment and the Trail Making Test. Neurocognitive testing will be performed preoperatively and on postoperative day 7. The Montreal Cognitive Assessment is a screening instrument for mild cognitive dysfunction, but it has also been used to assess cognitive functions in various neurological disorders, such as stroke, Parkinson’s disease, and multiple sclerosis [19–21]. It is suitable for the assessment of both distributed and focal cognitive domains, such as attention and concentration, executive functions, memory, language, visuoconstructional skills, conceptual thinking, calculation, and orientation. While the maximum test result is 30 points, a score of 26 is at the lower extreme of normal. As the patients in this study will be screened twice in a short period of time, we will use two versions of the test to negate the possible influence of a learning curve. A validated Croatian-language version is available for clinical and research purposes [22]. The Trail Making Test is a commonly employed neuropsychological instrument for evaluating visual attention, speed of processing and executive functioning [23]. It consists of two separate tasks, which evaluate the subject’s ability to alternate between cognitive categories [24]. In Part A, the subject is required to link randomly assigned numbers in ascending order. The goal in Part B is to link alternate numbers and letters in a pre-determined order (that is, 1-A-2-B…). The personnel responsible for neurocognitive testing will be unaware of the individual patient’s allocation to either the intervention or control arms.

### Neuroimaging

A comprehensive set of MRI sequences will be used for the analysis and quantification of structural and functional brain impairment following a standardized cardiac surgical procedure (Table 2). Patients with significant structural abnormalities identified on preoperative brain MRI (such as hydrocephalus, neurodevelopmental disorders, or brain tumors) will be excluded from the study. Magnetic resonance imaging will be performed twice in all patients (before cardiac surgery and on postoperative day 7) on a 3 T MR scanner (Magnetom TrioTim; Siemens, Munich, Germany) using a 32-channel head coil. To detect new structural ischemic lesions, pre and postoperative MRI exams will be compared for each patient. Fluid attenuated inversion recovery sequences (TR, 9000 ms; TE, 87 ms; voxel size, 0.9 × 0.9 × 4 mm,; field of view, 230 × 183; matrix, 204 × 256; flip angle, 130°) will be used to detect ischemic lesions and diffusion-weighted imaging sequences (TR, 3100 ms; TE, 92 ms; voxel size, 1.8 × 1.8 × 5 mm; field of view, 230 × 230; matrix, 128 × 128; b1,= 0 s/mm^2^; b2, 500 s/mm^2^; b3, 1000 s/mm^2^), together with calculated apparent diffusion coefficient maps, will be used to differentiate between old and new ischemic lesions. Regions of diffusion-weighted imaging hyperintensity and decreases in apparent diffusion coefficient correlate with acute ischemic brain injury [13], and will constitute a component of the primary endpoint measure. The volumes of new ischemic lesions will be calculated using Analyze 8.1 software (Mayo Clinic, Rochester, MN, USA). For rs-fMRI, gradient-echo echoplanar imaging sequences sensitive for blood-oxygen level dependent contrast will be applied (TR, 3000 ms; TE, 31 ms; voxel size, 3.4 × 3.4.3 mm; field of view, 220 × 220; matrix, 64 × 64; flip angle, 90°) for a period of 10 minutes and 8 seconds. Functional image data will be co-registered with high-resolution magnetization-prepared rapid acquisition gradient-echo T1 sequences (TR, 1900 ms; TE, 2.52 ms; voxel size, 1 × 1 × 1 mm; field of view, 250 × 250; matrix, 246 × 256, flip angle, 9°). The advantage of rs-fMRI lies in its ability to detect increases in the blood-oxygen level dependent contrast, as a measure of neural activity. Blood-oxygen level dependent signal variability is a surrogate measure of integrated synaptic activity [16]. All preprocessing, quality assurance, structural, and functional connectivity analyses will follow prior validated and published approaches that have been applied to clinical populations [25, 26]. Briefly, we will perform the following preprocessing steps for all blood-oxygen level dependent images, as previously described [25, 26]: (i) slice-time correction, (ii) first five images removed from each run, (iii) rigid-body motion correction, (iv) 12-parameter affine transform of the structural image to the Talairach coordinate system, and (v) coregistration of volumes to the structural image with 3 × 3 × 3 mm resampling.

**Table 2 Tab2:** **Summary of the MRI neuroimaging portfolio**

***MRI imaging sequences***	***Diagnostic target***
T1, T2, proton density signal weighting	Ischemic or hemorrhagic brain lesions.
	Structural brain abnormalities (hydrocephalus, neurodevelopmental disorders, brain tumors).
Magnetization-prepared rapid acquisition gradient-echo (three-dimensional)	Structural brain abnormalities.
	Anatomical three-dimensional template for subsequent rs-fMRI coregistration.
Fluid attenuated inversion recovery	Ischemic lesion of the brain parenchyma (acute, subacute, and chronic).
Diffusion-weighted imaging	Discrimination between acute, subacute, and chronic ischemic lesions, based on reduced diffusibility in acute or subacute lesions presenting as high signal on diffusion-weighted imaging sequence and low signal on calculated apparent diffusion coefficient maps.
rs-fMRI	Functional brain connectivity within neural networks. Comparison of functional connectivity patterns before and after operation.

MRI, magnetic resonance imaging; rs-fMRI, resting-state functional magnetic resonance imaging.

In addition, all blood-oxygen level dependent images will pass stringent quality assurance criteria to ensure that all data were of high and comparable quality across groups: (i) signal-to-noise ratios >100, computed by obtaining the mean signal and standard deviation for a given slice across the blood-oxygen level dependent run, while excluding all nonbrain voxels across all frames [1]; (ii) no blood-oxygen level dependent run with a single frame movement greater than one functional voxel; (iii) movement scrubbing [27, 28]. Lastly, to remove potential sources of spurious signal in resting-state data, additional preprocessing steps will be completed, according to standard practice [29]: all blood-oxygen level dependent time-series underwent high-pass (0.009 Hz) and low-pass (0.08 Hz) temporal filtering, nuisance signal removal from ventricles and deep white matter, global signal regression, six rigid-body motion correction parameters, and first derivatives using in-house MatLab tools [30].

### Outcome definitions

The primary composite outcome will consist of new ischemic lesions on brain MRI, impairment in brain connectivity on resting-state functional MRI (rs-fMRI) and postoperative cognitive dysfunction. Postoperative cognitive dysfunction will be defined as a decrease of at least one standard deviation in at least two components of neurocognitive testing.

The secondary endpoint measures will be:Volumetric quantification of areas of new ischemic lesions on structural brain MRI.Changes between pre- and post-rs-fMRI, expressed as continuous variables and compared among the intervention and control arms.Percentage declines in individual neurocognitive tests.Troponin T release on postoperative day 1.Incidence of major adverse cardiovascular events at 3 months postoperatively.

Major adverse cardiovascular events will comprise a composite endpoint measure, consisting of cardiovascular mortality, stroke, nonfatal myocardial infarction, and rehospitalization for ischemia. Perioperative myocardial infarction will be adjudicated in accordance to the definition supplied by the Joint European Society of Cardiology/American College of Cardiology Foundation/American Heart Association/World Heart Federation Task Force for the Redefinition of Myocardial Infarction [31]. Briefly, a troponin T value ten times the 99th percentile of the upper reference limit, coupled with electrocardiogram changes, new-onset coronary artery (or graft) occlusion, or imaging evidence of new wall motion abnormalities will meet the criteria for perioperative myocardial infarction [31]. Stroke will be a defined on the basis of either a new focal deficit lasting >24 hours or an imaging study suggestive of a new lesion in patients with prompt neurological recovery [32].

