## Background

Neurological impairment following coronary artery bypass grafting may take on the form of stroke or postoperative cognitive dysfunction. The former is rare, but potentially devastating. However, a decline in attention, memory, or fine motor skills can frequently be documented by sensitive neurocognitive testing [1]. Postoperative deterioration in neurocognitive capacity is often discrete, but exerts an adverse impact on the quality of life. Its reversibility is subject to interpatient variability, with 25% of patients still exhibiting signs of cognitive impairment 6 months after surgery [1, 2].

Ischemic preconditioning exploits the endogenous protective potential against sustained ischemia incurred by brief episodes of ischemia and reperfusion [3]. The phenomenon is probably triggered by both neuronal and humoral pathways [3]. In an experimental setting, transfer of coronary effluent from an ischemically preconditioned rabbit to an ischemic-preconditioning-naïve animal reduced myocardial infarct size in the latter [4]. This observation consolidated the hypothesis of a humoral protective mediator [4]. This hypothesis was corroborated by the induction of protection in a denervated donor heart by limb ischemia [5]. The fact that ischemic-preconditioning-induced organ protection was inhibited by a ganglion blocker, however, gave credence to the idea of the existence of underlying neural pathways [3].

Remote ischemic preconditioning (RIPC) denotes the concept by which brief episodes of sublethal ischemia in tissues with high ischemic tolerance stimulate protection in distant organs from a subsequent severe insult [6]. It is conceptually much simpler to induce than conventional ischemic preconditioning, thereby expanding its clinical applicability. Several reports have demonstrated that RIPC protocols lead to reductions in myocardial injury following cardiac surgery [7, 8]. Thielmann *et al.*
[9] recently showed that RIPC induced by upper limb ischemia in patients undergoing elective coronary artery bypass grafting led to a reduction in troponin T release, which mirrored an observed reduction in mortality (ratio, 0.27; 95% confidence interval, 0.08 to 0.98; *P* = 0.046).

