**Table 1 Tab1:** **Study inclusion and exclusion criteria**

*Inclusion criteria*	*Rationale for inclusion*
Adult patients (18 to 80 years) undergoing primary coronary artery bypass grafting with the use of cardiopulmonary bypass	Population of interest
***Preoperative exclusion criteria***	***Rationale for exclusion***
Emergent coronary artery bypass grafting	Higher-risk profile
Recent acute myocardial infarction	Concurrent indication for dual antiplatelet therapy
History of stroke or transitory ischemic attack	Prior neurological condition
Structural brain abnormalities	Prior neurological condition
Carotid artery disease	Ineligible for study enrollment
Valve surgery	Ineligible for study enrollment
Left ventricular ejection fraction <30%	Higher-risk profile
Atrial fibrillation	Higher-risk of neurological complications
Renal failure	Higher-risk profile
Repeat coronary artery bypass grafting	Higher-risk profile
Off-pump coronary artery bypass grafting	Avoidance of cardiopulmonary bypass
Inability to provide consent	Ineligible for study enrollment
Contraindications for MRI	Ineligible for study enrollment
Peripheral vascular disease of upper extremities	Contraindication for remote ischemic preconditioning
***Postoperative exclusion criteria***	***Rationale for exclusion***
New-onset contraindication for MRI	Protocol violation
Hemodynamic instability	Inability to complete follow-up MRI

MRI, magnetic resonance imaging.

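### Every primary component needs a day-7 scan or test score, so a clinical stroke or severe impairment that prevents assessment has no stated route to a primary event

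*Protocol article*

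**What the plan says.** **Primary outcome.** Under Outcome definitions, the Protocol article states: "The primary composite outcome will consist of new ischemic lesions on brain MRI", together with impaired connectivity on rs-fMRI and postoperative cognitive dysfunction. The cognitive rule is: "Postoperative cognitive dysfunction will be defined as a decrease of at least one standard deviation in at least two components of neurocognitive testing". The battery is the Montreal Cognitive Assessment and the two-part Trail Making Test.

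**Timing.** There is one postoperative assessment. Neurocognitive testing: "Neurocognitive testing will be performed preoperatively and on postoperative day 7". Neuroimaging: "Magnetic resonance imaging will be performed twice in all patients (before cardiac surgery and on postoperative day 7".

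**Image quality.** The criteria after Table 2 accept "no blood-oxygen level dependent run with a single frame movement greater than one functional voxel". This applies to the functional runs only.

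**Stroke and death.** Stroke is defined by a focal deficit lasting more than 24 hours, or by imaging in a patient who recovers promptly. It enters only the secondary composite at 3 months, as does cardiovascular death.

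**Removal after surgery.** Table 1 lists two postoperative exclusions: "New-onset contraindication for MRI", and hemodynamic instability, with the rationale "Inability to complete follow-up MRI".

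**The trial's own framing.** Background: "Neurological impairment following coronary artery bypass grafting may take on the form of stroke or postoperative cognitive dysfunction".

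**The concern.** Background names stroke and cognitive dysfunction as the two forms of neurological injury after this operation. The primary outcome reaches both only through what can be scanned or scored on day 7. A mild, measurable decline counts. A stroke that kills the patient on day 3, or leaves the patient unfit for testing and scanning, does not.

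These are the outcomes a neuroprotection trial most needs to capture. Whether the primary outcome can be observed depends on how bad it is, so the missingness is informative. If such patients are more frequent in one arm, the comparison of the remaining patients is biased.

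**Working it through.** **1. Routes to a primary event.** The article does not say whether one component suffices. The most generous reading, that any one does, is used here.

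| Patient, by day 7 | Structural lesion | Connectivity | Cognitive rule | Stroke definition |
|---|---|---|---|---|
| Stroke, dies before day 7 | no day-7 scan | no run | no score | met, secondary only |
| Stroke, can be neither scanned nor tested | no scan | no run | no score | met, secondary only |
| Too impaired to complete the tests, scanned, no lesion seen | negative | open if the run is usable; closed if it fails the movement limit | cannot be met if fewer than two components are scored | not necessarily met |
| Untestable, scanned, new lesion seen | met | – | – | – |

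The first two rows have no route. The third has none when the functional run is also unusable. The fourth does have a route.

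**2. What happens to them.** Statistical analysis names 2 × 2 tables and Fisher's exact test. It gives no class to a patient without a day-7 result. Table 1 removes some of these patients after randomisation.

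**3. The plan's sample size.** The inputs are an exact sign test, effect size 0.20, α 0.05 and power 0.90. If 0.20 means a probability of 0.70 against 0.50, two-sided, the smallest n reaching 0.90 is 65 (power 0.910). Exact power is jagged: it is 0.895 at 66, and only from 70 (0.922) does it stay above 0.90. The stated 70 is consistent with these inputs, but it includes an allowance whose rate is not given. That allowance names MRI contraindications and consent withdrawals, not deaths or untestable patients. This does not decide the point; 70 is used below only to set the arm size.

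**4. Weight of one patient.** Assume 1:1 allocation, so n = 35 per arm, with e true events.
- If scored as a non-event, the arm's rate falls by 1/n = 1/35 = 2.9 points.
- If dropped, it falls by e/n − (e−1)/(n−1) = (n−e)/[n(n−1)]. For e = 18 this is 17/(35×34) = 1.4 points; for e = 11, 24/1190 = 2.0 points; for e = 1, 34/1190 = 2.9 points.

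So 2.9 points is the ceiling under either handling.

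**5. Direction of bias if dropped.** Assume a true event risk of 50% in control and 30% with preconditioning (true difference 0.200), and that every unassessable patient is a true event. With a fraction m unassessable, the observed rate is (p−m)/(1−m).

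| Unassessable, control / RIPC | Observed rates | Difference |
|---|---|---|
| 5% / 5% | 0.474, 0.263 | 0.211 |
| 10% / 10% | 0.444, 0.222 | 0.222 |
| 10% / 5% | 0.444, 0.263 | 0.181 |
| 15% / 5% | 0.412, 0.263 | 0.149 |
| 5% / 10% | 0.474, 0.222 | 0.251 |

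With no true effect (50% in both arms), 15%/5% gives −0.062 and 5%/10% gives +0.029.

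**6. One assumed data set.** Events of 20/35 against 11/35 give Fisher p = 0.053. Dropping 4 and 1 unassessable events leaves 16/31 against 10/34, p = 0.081.

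**The case against.** The strongest reply is that this is silence on missing outcomes, which a condensed article may leave to the full protocol or analysis plan. That is right for imputation and for the analysis of missing scores. It does not cover what the article itself fixes: the three components, their single time point, and the placing of stroke in a secondary composite. An analysis plan could not make stroke a primary event without changing the stated endpoint.

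Several stronger readings are tempting, and the documents do not support them:
- **That these patients are scored as event-free.** No section says so. They are unclassified or excluded.
- **That a patient must both complete the tests and lie still.** These are separate routes. The movement limit applies to functional runs, and a new lesion on structural MRI counts without any test.
- **That such a stroke is lost altogether.** It still counts in the secondary composite.
- **That a delirious patient can never meet the two-component rule.** This assumes exactly three components: Montreal, Trail A and Trail B. The components are not listed, and the Montreal test spans several domains. The fatal or disabling stroke case does not depend on this.
- **That the shift can be set against a 20-point planning effect.** The 0.20 is a sign-test effect size, not a difference in risk between arms.
- **That the rule always hides a benefit.** Equal losses enlarge the difference in the table above.

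It is also fair that the trial enrols a lower-risk population and looks for subtle injury, so such patients may be few. That limits the size of the problem without removing it. Counting deaths from any cause as primary events would be a debatable change of endpoint and is not urged here.

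**Conclusion.** The point holds in limited form. As defined, the primary composite gives no route to an event for a patient with a clinical stroke who dies or can be neither scanned nor tested by day 7. Nor does it give one to a patient too impaired to complete the tests who has no detected lesion and no usable connectivity result. The loss depends on the outcome and can push the comparison either way.

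At an assumed 35 per arm, each such patient is worth at most about 2.9 points of that arm's rate. Under the assumed rates above, a true difference of 0.200 is observed as anything from 0.149 to 0.251. The documents give neither event rates nor the frequency of unassessable patients, so these figures show possible size and are not estimates. The change is worth making because it is cheap and stroke is already being recorded.

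**What to change.** Under Outcome definitions, state that:
- (a) clinical stroke by the definition already given, fatal stroke included, from randomisation to day 7 counts on its own as a primary composite event, and a Table 1 postoperative exclusion does not remove that patient from the primary analysis;
- (b) a cognitive component that cannot be completed on day 7 for a neurological or cognitive reason, as recorded by the blinded tester, counts as a decline of at least one standard deviation on that component. List the components, so that the two-component rule can be applied.

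Report non-stroke deaths before day 7 by arm, with a sensitivity analysis that counts them as events.

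The cost is a few sentences and one field on the test form for the reason a test was not done. Stroke is already collected for the secondary composite, and the testers are already blinded. The downside is that a few non-ischemic delirium cases will count as events; these can be listed separately.

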**Methods:**

Patients scheduled for elective coronary artery bypass grafting with the use of cardiopulmonary bypass will be screened for the study. Eligible patients will be randomized to undergo either a validated RIPC protocol or a sham procedure. The RIPC will be induced by inflation of a blood pressure cuff to 200 mmHg for 5 minutes, followed by a 5-minute reperfusion period. Three sequences of interchanging cuff inflations and deflations will be employed. Neurocognitive testing and MRI imaging will be performed preoperatively and on postoperative day 7. Paired pre- and postoperative neurocognitive and neuroimaging data will then be compared. The primary composite outcome measure will consist of new ischemic lesions on brain MRI, postprocedural impairment in brain connectivity on resting-state functional MRI (rs-fMRI), and significant new declines in neurocognitive performance. The secondary endpoint measures will be the individual components of the primary endpoint measures, expressed as continuous variables, troponin T release on postoperative day 1 and the incidence of major adverse cardiovascular events at 3 months postoperatively. Major adverse cardiovascular events, including accumulating cardiovascular mortality, stroke, nonfatal myocardial infarction, and rehospitalization for ischemia, will form a composite endpoint measure.

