### Sample size

The estimation of the approximate sample size for this study was based on an exact sign (binomial) test, assuming an effect size of 0.20. To account for potential postoperative contraindications for MRI and study consent withdrawals, an estimated 70 patients will be required to test the null hypothesis with an α value of 0.05 and a power of 0.90 [18].

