### Statistical analysis

The frequency distributions of primary and secondary study endpoints will be compared across the groups using 2 × 2 contingency tables. Continuous data will be presented as mean values ± standard deviation or medians with their respective interquartile range. Categorical variables will be presented as absolute numbers with percentages. Measures of association of categorical data will be derived from Fisher’s exact test. Analysis of continuous data will rely on the Mann-Whitney *U* test or Student’s *t* test. Comparisons of functional connectivity between regions of interest on pre- and postoperative rs-fMRI will be performed with the Wilcoxon matched-pairs test. Correlations between multiple variables of interest will be examined using Spearman’s or Pearson’s correlation coefficients. The choice between parametric and nonparametric statistical tools will be based on the normality of distribution. A two-tailed *P* value of less than 0.05 will be considered significant for all deployed statistical calculations. The data will be processed using the IBM SPSS Statistics software package (version 20.0; Somers, NY, USA).

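### Secondary cognitive and connectivity endpoints are compared as unadjusted percentage declines and changes, so the preoperative value every patient has is used inefficiently

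*Protocol article*

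**What the plan says.** All references are to the protocol article.

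- **Outcome definitions.** One secondary endpoint is "Percentage declines in individual neurocognitive tests". Another is the change between the pre- and postoperative resting-state scans, treated as continuous and compared between arms. No percentage scale is given for connectivity.
- **Neurocognitive testing.** "Neurocognitive testing will be performed preoperatively and on postoperative day 7". The instruments are the Montreal Cognitive Assessment (MoCA, maximum 30) and the Trail Making Test (TMT), parts A and B.
- **Neuroimaging.** Every patient is scanned before surgery and again on day 7.
- **Statistical analysis.** "Analysis of continuous data will rely on the" Mann-Whitney U test or Student's t test. "The choice between parametric and nonparametric statistical tools will be based on the normality of distribution". Regional connectivity before and after surgery is compared with the Wilcoxon matched-pairs test. No covariate or adjusted model is named.
- **Sample size.** "an estimated 70 patients will be required to test the null hypothesis with an α value of 0.05 and a power of 0.90".

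**The concern.** Each of these endpoints comes with its own preoperative measurement, usually the strongest single predictor of the day-7 value. A change score subtracts the whole baseline, as if the pre/post slope were 1. A percentage change divides by it, which puts baseline measurement error in the denominator. Neither estimates how much of the baseline carries over, so both leave avoidable variance in the arm comparison, and part of any chance baseline imbalance stays in the estimate. With 70 patients, that lost precision matters.

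Percentage change is also asymmetric. If TMT is scored as completion time, 40 to 80 s is +100% and 80 to 40 s is −50%. Two patients with exactly opposite ratios then average +25%.

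For connectivity there is a separate mismatch. The only test named specifically for it is a within-patient test, whereas the endpoint is a comparison between arms.

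**Working it through.** **Inputs.** From the article: 70 patients, two-sided 0.05, two arms, paired measurements. Assumed because the article does not give them: 1:1 allocation without losses (35 per arm), equal variances before and after surgery, correlation ρ, and a 0.5 SD effect for illustration.

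**The plan's own figure.** The sample size is "based on an exact sign (binomial) test, assuming an effect size of 0.20". Reading this as 0.70 against 0.50, two-sided, the smallest N with power of at least 0.90 is 65 (power 0.910). With an assumed 5% loss, 65/0.95 = 68.4, so 69; with 7%, 65/0.93 = 69.9, so 70. The stated 70 is reproduced on that reading. It says nothing about power for the continuous secondary endpoints.

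**Variance of the arm comparison, relative to the day-7 value alone (= 1).**

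- Change score: 2(1 − ρ)
- ANCOVA: 1 − ρ²
- Ratio, ANCOVA to change: (1 − ρ²)/[2(1 − ρ)] = (1 + ρ)/2

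| ρ | Change | ANCOVA | Ratio | ANCOVA N equal to 70 on change | Power, change | Power, ANCOVA |
|---|---|---|---|---|---|---|
| 0.3 | 1.40 | 0.91 | 0.65 | 45.5 | 0.42 | 0.59 |
| 0.5 | 1.00 | 0.75 | 0.75 | 52.5 | 0.55 | 0.68 |
| 0.7 | 0.60 | 0.51 | 0.85 | 59.5 | 0.77 | 0.83 |
| 0.8 | 0.40 | 0.36 | 0.90 | 63.0 | 0.91 | 0.94 |

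For ρ of 0.5 to 0.8 the gain is 70 − 52.5 = 17.5 down to 70 − 63 = 7 patients. This formula applies directly to connectivity, which the article states as a change.

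**Chance imbalance.** The standard error of the baseline difference is √(2/35) = 0.24 SD. Given a baseline difference D, the change score is shifted by (ρ − 1)D. An imbalance of one standard error therefore moves the estimate by 0.5 × 0.24 = 0.12 SD at ρ = 0.5, or 0.2 × 0.24 = 0.05 SD at ρ = 0.8. ANCOVA removes this shift.

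**Percentage decline.** The formula does not cover a percentage scale, so the planned analysis was simulated (3000 runs per setting). Percentage change was tested by t test if Shapiro-Wilk did not reject in either arm, otherwise by Mann-Whitney. The normal score had baseline mean 26 and SD 3, uncapped. The skewed score was lognormal with baseline median 100 and log-SD 0.45.

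| Score | ρ | Percentage decline, test chosen on normality | ANCOVA, raw | ANCOVA, log |
|---|---|---|---|---|
| Normal | 0.5 | 0.557 | 0.657 | – |
| Normal | 0.7 | 0.756 | 0.811 | – |
| Normal | 0.8 | 0.894 | 0.915 | – |
| Skewed | 0.5 | 0.515 | 0.607 | 0.647 |
| Skewed | 0.7 | 0.732 | 0.740 | 0.809 |
| Skewed | 0.8 | 0.886 | 0.879 | 0.922 |

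The gain is 10.0, 5.5 and 2.1 points for the normal score, and 13.2, 7.7 and 3.6 points for the skewed score on the log scale. With no effect, the normality-chosen procedure rejected in 0.041 to 0.058 of runs.

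**The case against.** Several points on the other side stand.

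- **Scope.** These are secondary endpoints. The primary composite is compared by a 2 × 2 table and is unaffected. Randomisation keeps the unadjusted comparison valid, so no bias or error inflation is shown.
- **Rank invariance.** Percentage change is post/pre − 1, a monotone function of the log ratio. Mann-Whitney gives the same result on either scale, so the asymmetry affects only a t test or reported means.
- **Raw-scale ANCOVA is not always better.** For the skewed score at ρ of 0.7 and 0.8 it was level with percentage decline (0.740 against 0.732; 0.879 against 0.886). There the gain comes from adjusting on the log scale.
- **Unseen plan.** The article condenses a fuller protocol, and covariate adjustment is often left to an analysis plan. However, the article does state the endpoint scale and the tests, so these are choices made rather than silence.

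A reader might also infer more than the article supports:

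- *That connectivity is analysed as a percentage.* It is stated only as a change.
- *That the baseline is thrown away.* Change and percentage change both use it. A comparison with unadjusted day-7 values would overstate the loss, because the plan does not use them for these endpoints.
- *That percentage decline is worse than a simple change score.* In the simulation it was level for the normal score (0.557 against 0.556 at ρ = 0.5) and slightly better for the skewed one (0.732 against 0.679 at ρ = 0.7).
- *That choosing the test on normality inflates type I error.* It stayed close to 5%.

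**Conclusion.** The point holds as an efficiency matter. Unadjusted comparison of percentage declines and raw changes gives up precision that the collected baselines could supply. The size is 10 to 25% of the variance of a change score for ρ of 0.5 to 0.8, and about 2 to 13 power points against percentage decline. The loss is larger if ρ is lower and almost vanishes as ρ approaches 1.

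These figures rest on assumed values of ρ, effect, variances and allocation. The normal-score simulation also ignores the MoCA ceiling of 30, so its gains are indicative.

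The within-patient Wilcoxon test cannot deliver the between-arm connectivity comparison that the endpoint definition promises. The general rule for continuous data can, but the article does not connect the two.

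This is a modest, nearly free improvement to secondary endpoints and does not threaten the trial's main conclusion.

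**What to change.** - In Outcome definitions, replace percentage decline as the tested quantity with the day-7 value of each test. Keep percentage decline as a descriptive summary.
- In Statistical analysis, state that day-7 MoCA total, log TMT-A, log TMT-B and each connectivity measure used will be compared by ANCOVA with arm and preoperative value as terms, reporting the adjusted arm difference and 95% CI.
- State that the Wilcoxon matched-pairs test describes within-patient change only and that the between-arm connectivity comparison comes from the ANCOVA.
- Optionally, fix in advance the tests for new-lesion volume and troponin T instead of choosing them on normality. This settles beforehand which quantity is reported; no error inflation was shown.

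The cost is analysis wording, with no new data, visits or patients. One piece of preparation is needed: the article names no network or region, so the connectivity measures have to be listed before analysis unless a fuller plan already does so. Recruitment was ongoing at publication.
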